#### ATI or continue ART phase

After the baseline imaging visit, participants will be randomized 1:1 to either continue their ART regimen or undergo ATI, to begin 2 weeks (±3 days) after baseline. This interim serves two purposes: (1) to give ATI participants time to recover so they can be biopsied from the same site again if indicated, and (2) for those on ATI who take NNRTIs, to switch to a protease inhibitor or an integrase inhibitor–based regimen to ensure that the washout period of ARV drugs is roughly equal. The study team will work with the participant's regular care team to adjust ART regimens as needed and oversee the ATI. If necessary to ensure a safe discontinuation of ART, the interval between baseline and ATI initiation may be lengthened up to 8 weeks. ATI participants will have a second set of imaging and biospecimen collection 7–13 days after starting ATI. A biopsy reviewer who is blinded to cohort assignment (ATI or continuing ART) will review the whole body PET/CT images and determine what sites to biopsy.

Participants on ATI will have weekly study visits to monitor HIV symptoms, viral load, and CD4 count. When the participant meets a restart criterion, including reaching 90 days of interruption even if no other criterion is met, they will resume their ART at the next weekly visit. This ART restart visit will include a research blood draw. As this blood draw is critical to the study goals, participants who do not return for their ART restart visit will be replaced. Participants who withdraw prior to achievement of ART resumption criteria will similarly be replaced. However, their data will be kept as it can be used in the PET/CT and biopsy timing analyses. They will be advised on resuming their ART at home and will be followed for safety.

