### Imaging HIV-infected individuals

Traditional histologic, immunohistochemical, and molecular approaches to identify and characterize lymphoid tissue prior to and following introduction of ART are challenged by difficulties in routinely obtaining such tissues. Non-invasive imaging modalities have been explored to characterize HIV infection, persistence, and reactivation following ATI. PET is an imaging modality that is useful for localizing and quantifying sites of increased metabolic activity, which are generally over-represented in neoplastic or inflammatory/infectious processes. The radionuclide tracer F-18 FDG is an analog of glucose that is readily taken up into cells that are actively metabolizing glucose. FDG is typically transported by GLUT-1 and GLUT-3 (20) transporters, and undergoes phosphorylation by hexokinase to FDG-6-phosphate, however it does not undergo further metabolism, but accumulates in cells instead (21–23). FDG accumulates in tumor cells, macrophages, and other immune cells and granulation tissue. FDG-PET of healthy individuals demonstrates a physiologic biodistribution involving increased uptake in the brain and liver and excretion through the kidney; uptake in the heart is variable depending on the myocardial energy substrate (24). Studies of individuals with HIV infection have shown FDG-PET activity in the CNS, even in individuals with suppressed viremia (25, 26). Extensive studies of FDG-PET imaging in the setting of rebound viremia have not been performed to confirm that increased uptake represents local viral replication or to characterize contributing viral populations.

Activated lymphocytes and neutrophils also utilize high levels of glucose, comparable to that of malignant cells. FDG-PET has accordingly been explored for localizing sites of infection and in the evaluation of individuals with fever of unknown origin. In evaluation of individuals infected with HIV, FDG-PET is effective for distinguishing the discrete lesions of CNS lymphoma from cerebral toxoplasmosis, which may appear similar by computed tomography (CT) and magnetic resonance imaging (MRI). Using PET scans, the high metabolic activity of CNS lymphoma (FDG-avid) is typically distinguishable from the low metabolic activity appearance of toxoplasmosis (FDG-non-avid).

PET has also been used to identify sites of inflammation in various non-HIV conditions, such as vasculitides, osteomyelitis, and sarcoidosis (27).

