**Primary**		
To evaluate if changes in glucose metabolism (as measured by FDG-PET SUV) correlate with changes in levels of HIV RNA in lymphoid tissue before and after ATI	Proportion of participants who have a 3-fold increase in HIV RNA levels in tissue sites identified by imaging as having increased SUV on FDG-PET as defined below	There are limited data on sensitivity of FDG-PET to detect HIV-infected cell populations during ATI. We will determine utility of this approach for investigating HIV persistence in people living with HIV

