#### Baseline/First imaging visit

At baseline, blood will be drawn *via* venipuncture for clinical and research evaluations, and participants will undergo whole body FDG PET/CT. Within the next 5 days, PBMCs will be collected by leukapheresis, and lymphoid tissue biopsies will be taken on the basis of imaging results. Approximately 2–5 biopsies will be performed after each PET scan. PET-avid (“hot”) and non-avid (“cold”) areas will be sampled. Lymph node biopsies will be guided by the combination of modalities most appropriate for each biopsy, which may include CT, ultrasound, and anatomic landmarks. Approximately 3 needle passes are typically performed, with the exact number guided by cytology feedback, intra-procedural factors, maintenance of low-risk, and size of target. Hot and cold nodes will be biopsied based on accessibility, with consideration for prior biopsies and consistency in biopsy site across participants. Optional sample collections are bone marrow biopsy, CSF *via* LP, and vaginal fluid or semen samples (which may be collected at home for the participant's convenience). Research evaluations on the samples are described in Table 2.

**Table 2 T2:** Biospecimen evaluations.

**Samples to be collected**	**Collection method**	**Study requirements**	**Analyses planned for samples (assuming sufficient material obtained)**
Peripheral whole blood	Venicpuncture	Required	• Human leukocyte antigen (HLA) testing • Collection of PBMCs • Characterization of HIV populations • Sequencing of HIV-1, including ARV resistance testing • Inflammatory markers/cytokine profiling • Soluble markers of immune response • ARV drug levels • Interferon gene variant analysis • Storage for future research
Peripheral leukocytes	Leukapharesis	Required	• T-cell repertoire • Characterization of HIV populations • Sequencing of HIV-1, including ARV resistance testing
Cerebrospinal fluid	Lumbar puncture	Optional	• Albumin • Quantitative amino acids • Glucose • IgG • Total protein • Cell count and differential • Blood • HIV quantitative PCR • HIV sequencing • Cytokine analysis • Storage for future research

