## Measures to minimize bias: Randomization and blinding

Randomization will be completed after study enrollment and will be 1:1 ATI to control (maintain ART). Image reviewers and biopsy reviewers will be blinded to randomization assignments until all 12 participants have completed the protocol and results have been analyzed as described in statistical considerations. The imaging reviewer is blinded as part of the determination of whether this study will be repeated. The biopsy reader is blinded to minimize bias in choosing which “hot” or “cold” nodes to biopsy. A Clinical Center (CC) staff radiologist who is not the blinded radiologist will review the PET/CT scans as they come in for clinical review and identification of sites to biopsy. As the ATI group will have three scans and the non-ATI group will have two scans, scans will be de-identified, and the first two scans will be used for discrimination of ATI vs. non-ATI to preserve blinding.

Randomization will be done by the Biostatistics Research Branch of the National Institute of Allergy and Infectious Diseases (NIAID). The randomization code will be maintained by the Biostatistics Research Branch on secure servers. The randomization code will be shared with all study staff except the blinded imaging and biopsy reviewers during the course of the study. Randomization will be performed *via* block randomization.

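### Nodes biopsied after the first scan are re-imaged far sooner in the ATI arm than in controls, and the protocol article gives no rule for reading uptake in them

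*Protocol article*

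**What the plan says.** All references are to the protocol article.

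- **Biopsy after scan 1** (Baseline/First imaging visit). "Within the next 5 days, PBMCs will be collected by leukapheresis, and lymphoid tissue biopsies will be taken on the basis of imaging results". About 2–5 biopsies follow each scan, and for each "Approximately 3 needle passes are typically performed".
- **Interval to ATI** (ATI or continue ART phase). ATI is "to begin 2 weeks (±3 days) after baseline". Two reasons are given: "to give ATI participants time to recover so they can be biopsied from the same site again if indicated", and time to switch participants off NNRTIs. As an exception, "the interval between baseline and ATI initiation may be lengthened up to 8 weeks".
- **Scan 2.** ATI participants are re-imaged on ATI days 7–13. Controls are re-imaged 12–16 weeks after their first scan (Resume ART phase or continue ART phase).
- **Tracer** (Imaging HIV-infected individuals). "FDG accumulates in tumor cells, macrophages, and other immune cells and granulation tissue".
- **Blinded classification** (Measures to minimize bias). "the first two scans will be used for discrimination of ATI vs. non-ATI to preserve blinding".
- **Primary endpoint** (Table 1). The proportion of participants with a 3-fold HIV RNA increase in "tissue sites identified by imaging as having increased SUV on FDG-PET".
- **Site choice.** Prior biopsies are considered when nodes are selected, and another node, preferably in the same region, may be used when the same site is not possible (PET/CT and biopsy timing justification). Both provisions concern which node to needle. Neither says how SUV in an already needled node is to be read.

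**The concern.** The study's own procedure injures the tissue it then images. The article names the kinds of cell and tissue that a healing needle site would be expected to contain as places where FDG collects, yet it treats the interval before ATI only as recovery time for re-biopsy and as time for a regimen change.

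Two uses of the second scan are exposed.

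1. **The blinded call.** The reader separates the arms on scans 1 and 2. If recently needled nodes light up, they do so mainly in the arm scanned early. A correct call could then reflect a recent biopsy rather than ATI. The result feeds the Fisher test and the criterion that moves imaging later if none of the six ATI participants is recognised.
2. **SUV-based site comparisons.** A node that is hot because it is healing enters the increased-SUV sites of the primary endpoint and the hot group of the hot/cold comparison. Repeat biopsy of the same site is envisaged, so nodes with their own baseline RNA value can be the ones sampled shortly before.

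The control arm was included to account for natural variation in FDG uptake. Scanned much later after biopsy, it does not measure uptake at the post-biopsy interval that applies to the ATI arm.

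**Working it through.** **Step 1. The plan's own test figure.** Sample size justification, one-tailed Fisher exact test, one misclassification in each arm:

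- 6 vs 6: (36 + 1)/924 = 37/924 = 0.040, as stated.
- 5 vs 5: (25 + 1)/252 = 26/252 = 0.103, as stated.

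**Step 2. Biopsy-to-scan-2 interval.** The article states none, so it is derived from the windows, counting scan 1 as day 0. Inputs: biopsy on day 0–5; ATI start on day 14 ± 3, that is 11–17; scan 2 on ATI day 7–13; control scan 2 on day 84–112. The shortest interval is earliest scan minus latest biopsy; the longest is latest scan minus earliest biopsy.

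| Situation | Shortest | Longest |
|---|---|---|
| ATI, standard | 11 + 7 − 5 = 13 days | 17 + 13 − 0 = 30 days |
| ATI, start delayed to 8 weeks | 56 + 7 − 5 = 58 days | 56 + 13 − 0 = 69 days |
| Controls | 84 − 5 = 79 days | 112 − 0 = 112 days |
| ATI, study repeated with scan at ATI days 3–6 | 11 + 3 − 5 = 9 days | 17 + 6 − 0 = 23 days |
| ATI, study repeated with scan at ATI days 14–17 | 11 + 14 − 5 = 20 days | 17 + 17 − 0 = 34 days |

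On the standard schedule the arms do not overlap: 79 − 30 = 49 days separate the latest ATI scan from the earliest control scan. Even at the 8-week limit the gap is 79 − 69 = 10 days.

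**Step 3. What a cue of unknown strength would do to the classification.** The documents give no duration or intensity of uptake after needle biopsy, so this step is purely illustrative. Assume that ATI itself has no visible effect, that no control is called ATI, and that each of six ATI participants is independently called ATI on healing uptake with probability q.

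With no control called, 3 of 6 ATI calls give p = 20/220 = 0.091 and 4 of 6 give p = 15/495 = 0.030. Significance at 0.05 therefore needs at least 4 calls.

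| q (assumed) | P(4 or more of 6 called) | P(1 or more called) = 1 − (1 − q)^6 |
|---|---|---|
| 0 | 0 | 0 |
| 0.10 | 0.1% | 47% |
| 0.25 | 3.8% | 82% |
| 0.50 | 34% | 98% |
| 0.75 | 83% | over 99.9% |

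A false significant result needs a high q. The none-recognised criterion is far more easily disturbed, because a single call prevents it from being met.

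**Step 4. Primary endpoint.** It requires raised SUV and a 3-fold RNA rise at the site. Healing may raise SUV; nothing in the article says that it raises HIV RNA. Spurious hot sites may contribute sites without an RNA rise, or may bring in sites whose RNA rose for other reasons. The text does not settle which dominates.

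**The case against.** The strongest reply is that the central premise is not documented. The article has one general background sentence on where FDG accumulates; it says nothing about needle biopsy, nor about how long or how intensely a sampled node stays avid. This stands: the effect may be nil at 13–30 days, and no size can be claimed.

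A reader might infer a size anyway. If 10–30% of sampled nodes were visibly healing, independently of each other, and none in controls, then 1 − (1 − q)^n gives 19–51% of ATI participants with at least one false hot node for two nodes, and 41–83% for five. Those percentages come entirely from the assumed rate. The documents equally allow a rate of zero, so they are no estimate of bias in this trial.

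Three further points have force.

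- Prior biopsies already enter site choice and other nodes may be substituted, so it is not a rule of the plan that every node with a baseline RNA value is a recently injured one.
- The RNA-based timing criteria do not depend on SUV, and the third ATI scan and the tissue studies are meant to help show what raised uptake represents.
- The article is condensed, and Supplementary material S1, which details the hot-spot analyses, is not shown. It may deal with sampled nodes.

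None of this removes the structural problem. The schedule and the choice of scans for the blinded reader are fixed in the article, and followed as written they leave a possible non-HIV cue that differs by arm. Equal scan timing would balance that cue, but would still leave recently needled nodes in the SUV–RNA and hot/cold comparisons.

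**Conclusion.** The concern holds as a structural weakness of unknown size. What is established from the text is the interval contrast (13–30 days against 79–112 days on the standard schedule, with up to 69 days for a delayed ATI start), the article's own statement on FDG in immune cells and granulation tissue, and the absence from the text shown of a rule for uptake in previously sampled nodes. It follows that healing uptake could be an arm-dependent cue for the blinded call and could add falsely raised sites to the SUV–RNA and hot/cold comparisons.

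Two stronger conclusions are tempting and not supported. One is that a large share of ATI participants will show false hot nodes; no document gives the rate. The other is that the primary endpoint is biased upward; it also needs a 3-fold RNA rise, so the direction is open.

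The point deserves action because a single call out of six can decide whether the none-recognised criterion is met, and because the check is cheap. It rests on the stated windows being followed and on Supplementary material S1 not already covering the matter.

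**What to change.** 1. Log each node and needle tract sampled after scan 1. Give the imaging reader locations only, without dates. All participants are biopsied at baseline, so the log does not reveal the arm.
2. Keep the planned blinded read. After it is recorded, have the same reader make a second call with the logged regions masked in both arms. Report the Fisher test and the none-of-six-recognised criterion for both calls.
3. Report the primary endpoint and the hot/cold comparison as planned, and again with sites sampled after the preceding scan excluded. Use baseline RNA from a same-region node where needed, a substitution the timing section already permits.
4. If Supplementary material S1 or the full protocol already contains such a rule, a cross-reference in the article's blinding and endpoint sections would do.

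The cost is a little more reading and analysis work. The companion analysis has fewer nodes and loses same-node pairs, which matters with six ATI participants, so it should sit beside the planned analysis rather than replace it. The same holds for the masked read, which removes real signal in the sampled nodes along with any artefact. The rules for choosing biopsy targets should stay as they are.

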#### Resume ART phase or continue ART phase

Participants who underwent ATI will continue weekly visits after ART restart, and will undergo a third and final set of imaging and sample collection within 21 days after achieving viral suppression (HIV RNA < 40 copies/mL) to facilitate understanding of what increased SUV represents (viral activity, generalized inflammation, or another process). The blinded biopsy reviewer will again determine what sites to biopsy on the basis of the whole body PET/CT images. Participants will also have the option to undergo additional lymph node biopsies on ART restart days 0, 5, and/or 10, if the lymph nodes are superficial and easily accessible for biopsy, as determined by the radiologist. Participation in this study for the ATI group ends after the third imaging visit. Supplementary Table S2 summarizes the schedule of events for ATI participants.

Participants who remained on ART will have a second and final set of imaging and lymph node biopsies at 12–16 weeks after the first, which is anticipated to correspond with the final imaging and sample collection of the ATI group. As with the ATI group, the blinded biopsy reviewer will determine what sites to biopsy on the basis of the whole body PET/CT images. Participation in this study ends after this visit. A third set of imaging and biopsies will not be pursued for those who remained on ART, because changes in PET or biopsy findings are unlikely and would be unnecessary procedures. Supplementary Table S3 summarizes the schedule of events for participants who continue ART.

After these initial 12 participants complete the study, an NIH Clinical Center (CC) staff radiologist on the study team will act as a blinded imaging reader to review the whole body PET/CT results and attempt to identify whether the participant continued their ART regimen or was on ATI. This is a different person from the blinded biopsy reviewer. The blinded imaging reviewer's success rate, and the data analysis described below, will determine if the study should be repeated to optimize timing of imaging and biopsy. A routine clinical read of the whole body PET/CT scans will also be performed by a CC staff radiologist unaffiliated with the protocol who is not blinded, and actionable results provided to the participant and/or care providers.

Initial data analysis will entail measurement of total HIV RNA by polymerase chain reaction (PCR) from lymph node biopsy specimens. Comparisons will be made between the ATI and continued-ART groups, as well as within each randomization group across time points. This analysis will be used to (1) determine if ATI participants vs. controls could be identified *via* PET/CT, and (2) determine if viral RNA in lymph nodes increased over the course of ATI. Based on the results of the analysis of this group, we may need to adjust the timing of the first PET/CT with biopsy after ATI; this change will be done through a protocol amendment. If it is determined after the first 12 participants that the timing of the first PET/CT with biopsy should be adjusted, according to criteria outlined under “PET/CT and Biopsy Timing Justification” (0–1 ATI participants has >3 fold increase RNA in a biopsy site OR none of the 6 ATI participants are correctly classified), then the study would be repeated with new participants and a modified schedule with the 2nd imaging and biopsy assessment moved to 14–17 days post-ATI. If all 6 have 3 fold tissue RNA increase, we will move the imaging and biopsy to 3–6 days post-ATI. The study would be repeated with the same number of participants. Data analysis would be repeated using the same criteria. The study may be repeated more than once, if needed. Additional repetitions would shift the imaging and biopsy by increments of 4 days.

Study visits will typically be done as outpatients, but participants may be admitted as inpatients at the discretion of the investigators.

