Upon introduction of ART, new virus transmissions to uninfected cells are effectively blocked. Viral RNA levels in blood decline as new cells are not being infected and infected cells are eliminated, either by direct viral killing or by immune-based mechanisms to eliminate virus-infected cells. Viral RNA levels in plasma decline as infected cells are eliminated by multimodal decay kinetics. A sharp initial decline of 10- to 100-fold in the first 1–2 weeks of therapy corresponds to loss of cells with a relatively short half-life (1–2 days) (5). This initial decline is followed by a second phase decline, with a characteristic half-life of 2–3 weeks, corresponding to the loss of longer-lived cells, including macrophages and long-lived CD4+ T cells. Within 1–6 months, viral RNA levels decline to a level less than that quantifiable by commercial HIV RNA detection. Use of sensitive single-copy HIV RNA detection assays has revealed HIV RNA levels undergo a third phase decline with a half-life of ~39 weeks, likely corresponding to long-lived cell compartments. Analysis of individuals undergoing long-term ART has revealed persistent viremia with no further decay detected after 3 to 4 years (6).

HIV-infected cells persist during therapy and are readily detectable using sensitive techniques. Viral RNA levels decline a median of 17,000-fold after introduction of ART, but cell-associated viral DNA declines only 10- to 30-fold, suggesting a substantial population of remaining virus-infected cells (7, 8). These quantitative studies only measure the presence of HIV DNA and do not detect or quantify levels of replication-competent virus. Other detailed studies have consistently demonstrated that the level of replication-competent HIV is only a small fraction (1–3%) of the total number of infected cells, as demonstrated by Chun et al. and Bruner et al. (9–12). HIV-infected cells are present in peripheral blood as well as diverse anatomic compartments, including secondary lymphoid organs [lymph nodes, spleen, and gut-associated lymphoid tissue (GALT)], central nervous system (CNS), and renal tissue, all of which may represent viral sanctuaries.

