## Discussion

HIV is controlled but not cured by combination antiretroviral therapy, and the mechanisms of HIV persistence remain poorly characterized. ATI studies have been useful in investigating the events in HIV rebound (71–77); many ATI studies analyze HIV present in plasma or in peripheral blood mononuclear cells. Most replication takes place in tissues, however, and HIV reactivation in tissues during ATI has not been well-studied. This protocol will allow us to explore utility of PET for identification of areas of high FDG uptake indictive of increased metabolic activity. By biopsying both FDG hot and FDG cold areas, we will be able to characterize these regions and investigate HIV replication during treatment interruption. One hypothesis is that PET SUV correlates with HIV viral RNA in biopsy of those regions and that lymph nodes with high SUV have higher viral RNA compared with areas with low SUV within a patient. If this is true, PET may be useful for identification of HIV infected cell populations, as well as monitoring response to cure strategies.

A randomized design was selected for this study to account for natural variation that might be seen in FDG uptake over time and to test the hypothesis that ATI engenders changes in FDG uptake not seen in patients who continue ART. Neither of these considerations could have been addressed without inclusion of the control ART continuation group. The possibility of doing only the ATI group, with each participant's baseline scan serving as their own control, was explored. Natural longitudinal variation in FDG uptake could, however, confound this approach. As Pfaehler and coworkers have reported, FDG PET uptake may be subject to variation from a number of potential sources (78, 79). Randomization to ATI vs. continuation of ART was necessary to optimize the balance of additional known and unknown confounders. The data generated, using rigorous uptake quantification, will also serve as an assessment of natural variation in FDG uptake over time, which will have general utility for FDG uptake studies.

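### In the blinded ATI-versus-control read, arm is completely aliased with scan interval: the second scan falls at day 18–30 (at most day 69) in the ATI arm and day 84–112 in controls

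*Protocol article*

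**What the plan says.** Timing in the ATI arm is set under *ATI or continue ART phase*. Interruption is "to begin 2 weeks (±3 days) after baseline", and then "ATI participants will have a second set of imaging and biospecimen collection 7–13 days after starting ATI". The same section allows a delay for safe discontinuation: "the interval between baseline and ATI initiation may be lengthened up to 8 weeks".

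Timing in controls is set under *Resume ART phase or continue ART phase*: "Participants who remained on ART will have a second and final set of imaging and lymph node biopsies at 12–16 weeks after the first". The reason offered for that window is a match with the other arm; it is a time "which is anticipated to correspond with the final imaging and sample collection of the ATI group". The control's second assessment is thus aligned with the ATI arm's third, not its second.

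The comparison itself is fixed under *Measures to minimize bias*. Because the arms have different numbers of scans, "the first two scans will be used for discrimination of ATI vs. non-ATI to preserve blinding". *Sample size justification* rests the 6 + 6 design on a one-tailed Fisher exact test of this read. The read also feeds the decision to repeat the study on a shifted schedule.

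The *Discussion* says that a randomised control was chosen to "account for natural variation that might be seen in FDG uptake over time", and that using each participant's own baseline was considered and set aside because longitudinal variation could confound it.

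**The concern.** A concurrent control removes time-related variation only if it is observed over the same stretch of time. Here the reader sets a change over about three to four weeks in one arm against a change over 12–16 weeks in the other. Anything that makes uptake change depend on elapsed time, or on time since 2–5 needle biopsies, differs systematically between the arms whether or not ART was stopped. No analysis can undo this, because no control is seen at the ATI interval and no ATI participant's second scan is seen at the control interval.

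At stake is what a significant or a null classification result means. That test is the basis of the sample size and one of the inputs to the repeat decision. The protocol also reasons in two directions. *Imaging HIV-infected individuals* and *Resume ART phase or continue ART phase* treat change in controls as unlikely, which justifies fewer scans, while the *Discussion* says such change cannot be assumed away.

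**Working it through.** **The plan's own figure.** With 6 per arm, six people called ATI and one wrong call in each arm, the table is [[5,1],[1,5]]. One-tailed p = (6×6 + 1)/C(12,6) = 37/924 = 0.040, as stated. With 5 per arm, (5×5 + 1)/C(10,5) = 26/252 = 0.103, as stated. The arithmetic is sound; the issue is what the test compares.

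**Day of the second scan, counted from the baseline scan**
- ATI start: 14 ± 3 = day 11–17.
- ATI arm, as scheduled: 11 + 7 = 18 to 17 + 13 = 30.
- ATI arm, longest permitted delay: 56 + 13 = 69.
- Controls: 12 × 7 = 84 to 16 × 7 = 112.
- Gap as scheduled: 84 − 30 = 54 to 112 − 18 = 94 days. The control interval is 84/30 = 2.8 to 112/18 = 6.2 times as long.
- Gap at the longest delay: 84 − 69 = 15 days. There is still no overlap.

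**Time from baseline biopsy to the second scan.** *Baseline/First imaging visit* places biopsies within 5 days of the scan.
- ATI arm, as scheduled: 18 − 5 = 13 to 30 days.
- Controls: 84 − 5 = 79 to 112 days.

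**Repeat schedules.** Moving the ATI assessment to 14–17 days post-ATI gives 11 + 14 = 25 to 17 + 17 = 34 (at most 56 + 17 = 73). Moving it to 3–6 days gives 11 + 3 = 14 to 17 + 6 = 23. Neither reaches day 84.

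**How sensitive the test is.** The documents give no drift or standard deviation for SUV change, so the shifts below are assumptions shown as a range. Simulation: 200,000 trials, normally distributed changes with equal SD, the six largest changes called ATI, success meaning at least five of the six ATI participants correctly called (p ≤ 0.04).

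| Assumed shift from interval alone (SD) | No ATI effect; ATI-arm change larger by the shift | True ATI effect of 2 SD; control change larger by the shift |
|---|---|---|
| 0 | 0.04 | 0.83 |
| 0.5 | 0.15 | 0.62 |
| 1.0 | 0.36 | 0.36 |
| 1.5 | 0.62 | 0.15 |

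Entries are the probability of success. The middle column is false-positive risk; the right-hand column is power.

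**The case against.** The layout is deliberate. The protocol says that uptake in people continuing ART should not change over a short period and that extra procedures would be unnecessary. Controls do record longitudinal variation, and the *Discussion* names no interval. If uptake on stable ART is flat, the mismatch does no harm. That possibility stands, and it is why no size can be put on the bias. It does not settle the matter, because the same stability would remove the reason given for having controls.

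Four stronger readings are tempting, and the documents do not support them.

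- *The reader could score 12 out of 12 (p = 1/924 = 0.001) with no HIV effect.* This needs a cue that separates the arms perfectly and a reader who uses only that cue. It is an upper bound, and it ignores that the bias may run the other way.
- *Healing at biopsy sites will mark the ATI arm.* The protocol notes that FDG accumulates in granulation tissue, so this is plausible. Nothing in it shows that needle-biopsy uptake persists at 2–4 weeks, and the two-week interim is partly meant for recovery.
- *The 12–16 week window misses the ATI arm's final scan.* One can build a range of about 12–40 weeks from the sustained-viraemia restart criterion and the statement "Within 1–6 months, viral RNA levels decline to a level less than that quantifiable by commercial HIV RNA detection". That statement describes first introduction of ART, not re-suppression. The other restart criteria allow an earlier finish: 11 + 14 + 28 = 53 days, about 8 weeks, on the same borrowed figures. The 90-day limit allows a later one: restart by day 17 + 90 + 7 = 114, then 26 weeks and 21 days, giving 317 days or about 45 weeks. The protocol claims only an anticipated match.
- *The between-arm tissue RNA comparison is equally compromised.* The interval mismatch applies there too, but participants have been suppressed for at least 3 years, and nothing shown suggests that nodal RNA on stable ART differs between about 3 and 14 weeks.

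**Conclusion.** The concern holds for the blinded classification. Arm is completely aliased with scan interval, by at least 54 days as scheduled and 15 days at the longest permitted delay, and with time since baseline biopsy. Controls measure natural FDG variation, but not over the interval at which they are compared with ATI participants, so the purpose stated in the *Discussion* is not met for this test. The assumption of no change in controls and the reason given for including them need to be reconciled.

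The bias may favour or mask an ATI effect, and it is zero if uptake change does not depend on interval or time since biopsy. The simulated figures rest on assumed shifts and show sensitivity only. The primary endpoint (read, as its objective implies, as a before-and-after-ATI measure) and the RNA retiming criterion use ATI participants only and are not affected. The PET recognition criterion comes from the same read, so it is. The aliasing cannot be repaired once participants have completed follow-up.

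**What to change.** Keep two scan and biopsy sets in controls, but schedule the second at the same interval from baseline as the ATI arm's second. To do this, record for every participant, in both arms, a notional ATI start date that applies the same window and any extension the participant would have needed. Count the second assessment from that date. If the study is repeated on a shifted schedule, the control assessment moves with it. Treatment and restart rules are untouched.

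As a sensitivity analysis, have the blinded reader repeat the classification disregarding nodes biopsied at baseline. This should not replace the main read, since it would discard sampled hot nodes.

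Cost: a protocol amendment to one research visit window and one extra read of existing images, with no additional participants, scans or biopsies. Control biopsies would fall closer together, at the spacing already planned for the ATI arm. The approximate control for the ATI arm's final scan is lost, so that scan would be interpreted within participant; the classification does not use it. The text on expected stability in controls and the text on why controls are needed should be aligned in the same amendment.
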